### Control group

The control (physical activity) group will receive the same six week physical activity intervention previously found to be efficacious [13,27]. Also based on social cognitive theory, it includes a pedometer and step recording calendar via mail and two behavioural coaching and goal setting sessions (on physical activity, and recommending 30 minutes of physical activity on most days of the week) via telephone as well as two booster phone calls after the intervention.

### Data collection

Questionnaires will be completed by telephone at baseline, eight weeks and eight months for the intervention group and at baseline, six weeks and six months for the control group. Researchers administering the questionnaires will be trained to follow written standard procedures. They will be supervised during the administration of the initial questionnaires and thereafter at random intervals. All objective measures will be obtained by the same researcher following a written standard protocol.

### Process evaluation measures

Semi-structured interviews will be conducted with urban and rural CR staff to assess their views of the usefulness and acceptability of the program and its implementation in their setting. Focus groups will be held with rural and urban study participants regarding their experiences of the program and its delivery. Participants will also provide information on process measures when they complete the telephone questionnaires at week eight (intervention) and week six (control) on the acceptability of program activities and materials such as resources on weight control, nutritional and physical activity, and coaching advice. The weight, nutrition and physical activity goals set by participants during their telephone coaching sessions will also be recorded.

### Outcome measures

The primary outcome is self-reported weight and BMI [3]. Secondary outcomes include self-reported physical activity, sedentary time and nutrition habits. The Active Australia Questionnaire [35], which has demonstrated validity in Australian community [36] and clinical populations [23,37], will be used to assess self-reported total physical activity per week. Sedentary time will be assessed using the question on usual week day sitting time from the International Physical Activity Questionnaire which also has demonstrated reliability and validity [38]. Nutrition habits will be assessed using questions on food intake from the NSW Population Health Survey [39]. Confidence, planning intentions and social support for healthy eating and physical activity will be assessed using questions adapted from previous studies [13,40-42]. Quality of life will be measured using the Assessment of Quality of Life (AQoL) questionnaire which measures quality of life in the domains of independent living, social relationships, physical senses and psychological wellbeing [43]. Quality Adjusted Life Years (QALYs) will also be calculated using the AQoL. The AQoL has been validated for telephone delivery [44] and uses utility weights derived from an Australian population [45].

To validate self-reported changes in height, weight, food intake and physical activity, objective data will be collected at baseline and at eight months from a sub-group of 25% of the intervention group (a convenience sample of 45 participants). At baseline and at eight months the researcher will meet with this sub-group to measure their height, weight and waist circumference after they have self-reported these measures in the questionnaires administered via telephone at baseline and eight months. Participants will then be asked to record their intake of food and drink for three days (two weekdays and one weekend day) and to wear an MTI Actigraph accelerometer to record their physical activity for the next seven days. At the end of the week in which the accelerometer is worn the self-report questions on physical activity, sedentary activity and nutrition habits, which ask about these activities over the last seven days, will be completed. Thus the objective data obtained using a food diary and accelerometer will be collected over the same time period as the self-reported data. A three-day food diary collected over two week days and one weekend day has been found to be a reliable measure of usual energy intake [46]. Accelerometry is a widely accepted method for measuring total movement and provides objective data on the frequency, intensity and duration of physical activity [47].

Costs calculated will include program costs (for example staff time, equipment and telephone costs), direct health care costs related to participants' cardiac conditions (for example emergency department visits, hospital admissions, day procedures, general practitioner and cardiac specialist visits) and other costs (for example participant's expenditure on exercise related products and services such as shoes and exercise classes). Information will be collected regarding the number of days absent from work or normal activities due to cardiac problems.

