### Randomisation and blinding

During the follow up telephone call participants will be randomised by the researcher into intervention and control groups when they agree to be enrolled in the study. Participants will be block randomized within site. Microsoft Excel will be used to generate random numbers and the Statistical Analysis System (SAS) will be used to randomise these numbers into sets of two letters (A and B, representing the intervention and control groups respectively) by blocks of four to ensure a balanced sample size across both study groups [31]. The random numbers will be generated and packaged by a person external to the study so the group allocation will be concealed from the researcher until the participant has agreed to be in the study [32]. Participants will not be told whether they have been allocated to the intervention or control group and will remain blinded to group allocation. Group allocation will not be concealed from the researcher when delivering the intervention or assessing outcomes.

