### Sample size

To detect a reduction of 1.3 kg in weight and 0.5 kg/m^2 ^BMI between the intervention and control group (based on the COACH study effects on weight loss [24]) with a power of 90% (alpha 0.01), adjusting for clustering, and assuming a 20% loss to follow up, a sample size of 178 in each group is required.

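### Measuring 45 intervention participants, and no described controls, between their baseline and later self-reports could bias the self-reported weight and BMI comparison

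*Protocol article*

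**What the plan says.** The Outcome measures section of the protocol article states: "The primary outcome is self-reported weight and BMI". Validation is confined to one arm: "objective data will be collected at baseline and at eight months from a sub-group of 25% of the intervention group", described there as a convenience sample of 45 people. No in-person measurement of controls is described.

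The order is fixed in the same section. At each of the two visits the researcher will "measure their height, weight and waist circumference after they have self-reported these measures in the questionnaires administered via telephone at baseline and eight months". The Data collection section sets the reporting times: "Questionnaires will be completed by telephone at baseline, eight weeks and eight months for the intervention group and at baseline, six weeks and six months", where the last three times are those of controls. So in the 45, the baseline report comes before any study weigh-in, and both later reports come after one.

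The Statistical analysis section compares the arms on all cases, adjusting for residence, age and sex. Membership of the measured sub-group is not among the adjustment variables.

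**The concern.** A steady reporting error cancels from a change score; one that shifts between baseline and follow-up does not. Reporting the weight first and measuring second protects the validation comparison at each visit. It does not protect the follow-up reports from the baseline weigh-in. Someone who learns at baseline that the scale reads higher than the figure given by telephone may report closer to the scale next time, and the correction then looks like weight gain.

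As described, a quarter of one arm is exposed to this and the other arm is not. The exposure arises after allocation, so randomisation does not balance it. Two things are at stake:

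- The arm difference in weight and BMI change could be shifted. The Economic analysis section calculates cost-effectiveness ratios only for statistically significant outcomes, so a missed weight effect would also lose its economic result.
- The sub-group's self-reported change may not represent that of the other 178 − 45 = 133 intervention participants, or of controls, whom the study does not measure. Validating change is the sub-group's stated purpose: "To validate self-reported changes in height, weight, food intake and physical activity, objective data will be collected at baseline and at eight months".

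**Working it through.** **Inputs from the documents.** 178 per group, 90% power, alpha 0.01, 20% loss and a 1.3 kg target (Sample size); 45 measured participants, all in the intervention arm (Outcome measures).

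**Inputs assumed.** The size and direction of self-report error, which the documents do not give; a two-sided alpha; equal loss in the sub-group and the rest; no change in reporting error among everyone else.

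**The plan's own figures.** The share reproduces: 45/178 = 25.3%, and 0.25 × 178 = 44.5. The 178 itself can be neither reproduced nor refuted, because the article gives no SD or design effect. It is not at issue.

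**Bias.** Let e be the baseline under-reporting and u the part of it removed because of the weigh-in.

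- Baseline report = true weight − e.
- Later report = true weight − (e − u).
- Reported loss = true loss − u in the sub-group, and true loss elsewhere.
- Shift in the arm difference = (45/178) × u = 0.253u, against the intervention when u is positive.

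**Standard error implied by the stated design.** Whatever SD and design effect were used, 90% power for 1.3 kg at two-sided 0.01 requires SE = 1.3/(2.576 + 1.282) = 0.337 kg.

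**Power.** Φ((1.3 − 0.253u)/0.337 − 2.576). The last column puts 1.960 in place of 2.576, because the Statistical analysis section uses 0.05.

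| Assumed u (kg) | Shift (kg) | Share of 1.3 kg | Apparent effect (kg) | Power, alpha 0.01 | Power, alpha 0.05 |
|---|---|---|---|---|---|
| 0 | 0 | 0% | 1.30 | 90% | 97% |
| 0.5 | 0.13 | 10% | 1.17 | 82% | 94% |
| 1 | 0.25 | 19% | 1.05 | 70% | 87% |
| 2 | 0.51 | 39% | 0.79 | 41% | 65% |

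If baseline under-reporting is 0.5 kg and only half is corrected (u = 0.25 kg), the shift is 0.06 kg and power at 0.01 is about 86%. Over-reporting at baseline makes u negative and inflates the apparent benefit by the same amounts.

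**BMI.** Height is also self-reported and then measured. If BMI uses each visit's reported height (not stated), correcting an over-reported height raises later BMI as well. At an assumed 80 kg and true height 1.70 m, a 1 cm correction gives 80/1.70² − 80/1.71² = 0.32 kg/m². Multiplied by 0.253, that shifts the arm difference by 0.08 kg/m², or 16% of the 0.5 kg/m² target.

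**Cost of leaving the 45 out.** After 20% loss, 0.8 × 178 = 142.4 controls and 0.8 × 133 = 106.4 intervention participants remain. SE ratio = √[(1/106.4 + 1/142.4)/(2/142.4)] = 1.081. Power = Φ(1.3/(0.337 × 1.081) − 2.576) = 84% at alpha 0.01.

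**The case against.** The strongest reply is that the mechanism needs participants to learn their readings, and the article does not say that they do. The Data collection section refers to a written standard protocol for objective measures, which is not shown and may settle this. If readings are withheld, or self-report is accurate on average, u is near zero. This stands, and it is why the point is a risk and why zero belongs in the range.

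It is also fair that the size is wholly assumed. The formula counts only correction due to the weigh-in. Intervention participants are coached on weight and set weight goals, so the other 133 may also report more accurately over time, and the weigh-in's added effect could be smaller than the baseline error. The exposure is diluted about fourfold, and in the under-reporting case it hides benefit and does not create it.

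A reader might infer that the trial's result is biased, that the weigh-in comes immediately after the telephone call, or that everyone else is never weighed. The documents support none of these. They say only that measurement comes after the self-report, give no reporting error, and are silent on weighing outside the study. Some participants will attend cardiac rehabilitation, and all need a doctor's clearance.

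A missing sensitivity analysis is not a fault here either, since that is commonly left to an analysis plan. What remains is the design that the article does fix: one arm only, with measurement between the baseline and later reports.

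**Conclusion.** The point holds as a risk of differential bias. By design, 25.3% of the intervention arm and no described controls are measured between the baseline and follow-up reports of a self-reported primary outcome. If readings reach participants, the arm difference shifts by 0.253 kg for each kilogram of baseline error that the weigh-in corrects: 0 to 0.51 kg over an assumed 0 to 2 kg, with power at alpha 0.01 running from 90% to 41%. The lower end applies if readings are not disclosed. The direction depends on whether baseline weight is under- or over-reported, which the documents do not say.

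Separately, the validation of change describes people who have already been measured and may not carry over to the rest of the trial. The remedy is a cheap improvement, and nothing here shows that the intention-to-treat result would be invalid.

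**What to change.** 1. State in the measurement procedure that sub-group participants are not shown or told their baseline scale and height readings until after their eight-month telephone self-report.
2. Beside the intention-to-treat result, report a supportive analysis of weight and BMI change that leaves out the 45. Label it non-randomised: the 45 are a convenience sample from one arm, so a difference from the main result may mix selection with anchoring.
3. State that the validation of change applies to people who have already been measured.

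The cost is one line of procedure, one analysis and one sentence of interpretation. Participants wait for their readings, which needs to fit with what they consent to. The supportive analysis has an SE about 8% larger (about 84% power at alpha 0.01). Measuring a random sub-sample in both arms would address the imbalance more directly, but needs more fieldwork.

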### Sample size

To detect a reduction of 1.3 kg in weight and 0.5 kg/m^2 ^BMI between the intervention and control group (based on the COACH study effects on weight loss [24]) with a power of 90% (alpha 0.01), adjusting for clustering, and assuming a 20% loss to follow up, a sample size of 178 in each group is required.

### Statistical analysis

The analyses of the trial will be based on (i) intention to treat and (ii) treatment received. Bivariate and multivariate analyses will assess the effects of the intervention (compared to controls) on weight loss, sedentary behaviour, nutrition and physical activity adjusted for residence (rural or urban), age and sex for all cases and then treatment received after initial intention to treat analysis. Continuous data will be analysed with paired t-tests and linear regression and categorical variables with chi square tests and logistic regression with p < 0.05 as the level of significance but adjusted appropriately when multiple testing is conducted. Analyses will be performed with PASW 18.0 (SPSS Inc., Chicago, IL). Food diaries will be analysed using FoodWorks 2007 (Xyris Software).

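### The methods named for weight and BMI do not by themselves deliver the promised all-cases intention-to-treat analysis under the 20% loss the plan assumes

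*Protocol article*

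**What the plan says.** Three parts of the protocol article bear on this.

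- **Statistical analysis.** The trial is to be analysed by intention to treat and then by treatment received. The effects on weight and the other outcomes are adjusted for residence, age and sex on all cases. The methods for continuous outcomes are then named: "Continuous data will be analysed with paired t-tests and linear regression".
- **Sample size.** The calculation ends: "assuming a 20% loss to follow up, a sample size of 178 in each group is required". The target is a difference of 1.3 kg in weight and 0.5 kg/m² in BMI, "with a power of 90% (alpha 0.01), adjusting for clustering".
- **Data collection.** "Questionnaires will be completed by telephone at baseline, eight weeks and eight months for the intervention group". Controls are also interviewed three times, the second time at six weeks and the third at six months. Each arm therefore has an early and a late follow-up weight.

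The Outcome measures section names self-reported weight and BMI as the primary outcome without attaching a time point. The article mentions no repeated-measures model and no imputation. It also states no restriction to people with complete data.

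**The concern.** A paired t-test needs both members of the pair. An ordinary linear regression of late weight, or of change to late weight, omits anyone whose late weight is missing. Used as named on the late follow-up, neither method can include the one in five people the plan expects to lose. Neither makes any use of the early weight that some of those people will have given. The stated principle (intention to treat, all cases) and the stated tools therefore do not match.

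The design gives reasons to think that loss could differ between arms. The last contact is two months later in the intervention arm. That arm is coached on weight in four sessions, while the control arm is coached only on physical activity in two. Weight is self-reported by telephone, so someone coached to lose weight who has not done so may be less willing to take the last call. These are plausible mechanisms, not facts in the article.

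If they operate, the people still present in the intervention arm look better than the arm as a whole, and the estimate favours the intervention. The error could carry into the Economic analysis section, where cost-effectiveness ratios are calculated only for statistically significant outcomes and weight effects are extrapolated to long-term outcomes.

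**Working it through.** **Inputs from the article.** 178 per arm, 20% loss, target 1.3 kg, 90% power, alpha 0.01. The article gives no SD, no size for the clustering adjustment and no sidedness for alpha. I take alpha as two-sided.

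**The plan's own figure.** Without an SD, 178 cannot be reproduced independently, so I solved backwards for the SD.

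- Analysable per arm: 178 × 0.8 = 142.4. Lost: about 36 per arm, 71 of 356 in all.
- SD = 1.3 × √(142.4 / (2 × DE)) / (z₀.₉₉₅ + z₀.₉₀), with z₀.₉₉₅ + z₀.₉₀ = 2.576 + 1.282 = 3.857 and DE the design effect.
- DE 1.0 gives SD 2.84 kg, DE 1.2 gives 2.60 kg, and DE 1.5 gives 2.32 kg.
- Forward check at SD 2.84 kg and DE 1: n = 2 × 3.857² × 2.84² / 1.3² = 142.02, rounded up to 143. Then 143 / 0.8 = 179, one away from 178. This is a back-fit, not a confirmation.

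**Bias, illustration A: informative loss in the intervention arm only.** Suppose a latent tendency to stay in the study has correlation r with weight loss in the intervention arm and none in the control arm, and that 20% are lost in each arm. The mean among those retained is shifted by r × SD × φ(z₀.₈) / 0.8. Here φ(0.842) = 0.280, and 0.280 / 0.8 = 0.35.

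| r | SD 2.84 kg (DE 1) | SD 2.32 kg (DE 1.5) |
|---|---|---|
| 0.1 | 0.10 kg | 0.08 kg |
| 0.2 | 0.20 kg | 0.16 kg |
| 0.3 | 0.30 kg | 0.24 kg |

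Against 1.3 kg, the first column is 8% to 23% and the second 6% to 19%.

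**Bias, illustration B: leavers do worse by the same amount g in both arms.** The completers' contrast is off by (d₁ − d₀) × g, where d₁ and d₀ are the proportions lost in the intervention and control arms.

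| Loss, intervention v control | g = 1 kg | g = 2 kg | g = 3 kg |
|---|---|---|---|
| 20% v 20% | 0 | 0 | 0 |
| 25% v 15% | 0.1 kg | 0.2 kg | 0.3 kg |
| 30% v 10% | 0.2 kg | 0.4 kg | 0.6 kg |

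**Precision recovered by using the early weight.** Let n_c = 142 be the number with a late weight, n₂ = 36q the number with an early weight only, and ρ the correlation between early and late change. Under missing at random, effective n = n_c / [1 − ρ² × n₂ / (n_c + n₂)]. The values of q and ρ are assumed; neither is in the article.

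- q = 0.25, ρ = 0.5: 142 / (1 − 0.25 × 9/151) = 144, power 90.5%.
- q = 1, ρ = 0.8: 142 / (1 − 0.64 × 36/178) = 163, power 94.0%.
- For comparison, at SD 2.84 kg and two-sided alpha 0.01, power is 90.0% with 142 per arm and 96% if all 178 had a late weight.

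**The case against.** The strongest reply is that the article never says that people without a late weight will be excluded. Linear regression can follow multiple imputation or another rule for missing values, and a condensed article commonly leaves that rule to the full protocol or analysis plan. This stands in part. A reader might infer that the trial has chosen a completers' analysis and labelled it intention to treat; the text does not support that. Nor does inflating the sample for 20% loss show it, because imputation and mixed models also lose information when outcomes are missing. What remains is narrower. The article names specific tools next to an all-cases promise, and those tools alone do not keep it.

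Further objections also stand:

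- No primary time point is given. A comparison at the early follow-up would use the early weights, so it cannot be said outright that they are discarded.
- The number of leavers who would have an early weight is unknown. Anyone lost before the early call has nothing to recover.
- Illustration A sets informative loss to zero in controls, which guarantees a one-sided bias. Illustration B shows zero bias when loss is equal and equally informative.
- A model that assumes missing at random removes only the part of the bias explained by observed data. Avoiding the last call because of a disappointing weight may not be fully explained by the early weight.
- A reader might suppose that people who stop coaching will no longer be called for assessments. Nothing in the article says so.

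**Conclusion.** The point holds in limited form. Under the 20% loss that the plan assumes, paired t-tests and linear regression applied as named to the late follow-up would use about 142 of 178 per arm and ignore the early weights of later leavers. That does not meet the stated all-cases intention-to-treat principle.

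The consequence is a possible bias, not a demonstrated one. The 0.1 to 0.3 kg illustration needs retention to correlate 0.1 to 0.3 with weight loss in the intervention arm alone, and an SD back-solved with no design effect. At a design effect of 1.5 it is about 0.08 to 0.24 kg. It would be wrong to read 8% to 23% of the target as an expected bias, or as the amount a better model would remove. The gain in power, from 90.0% to between 90.5% and 94.0%, is too small to be the reason for change. The reason is that the repair uses data already scheduled, costs little, and brings the method into line with the stated principle.

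**What to change.** For weight and BMI, make the primary between-arm analysis one of the following:

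- a likelihood-based repeated-measures model with both scheduled follow-ups as outcomes, and arm, visit, arm-by-visit, baseline value, residence, age and sex as terms; or
- the planned linear regression after multiple imputation, with the early weight in the imputation model.

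Given the same variables, the two serve the same purpose. State that the visits are nominal (early and late), because their timing differs by arm: eight v six weeks, and eight v six months. Say which visit supplies the primary contrast.

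Add one delta-adjusted sensitivity analysis in which intervention leavers are assumed to have lost less weight than the model predicts, over a range fixed in advance.

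The cost is a few lines of wording and modest extra analysis, with no new data and no change to 178 per arm. The downside is reliance on missing at random, which corrects only loss explained by observed data. The delta analysis shows how far the result depends on it. People with no follow-up weight at all still add essentially no information, and the plan should say so.

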### Participants

All people referred to outpatient CR over a 12-18 month period at two Sydney and two NSW rural hospitals in Australia will be invited to participate in the study, whether or not they attend outpatient CR. Based on a previous Australian study [13], it is anticipated that of those invited to the study 29% will attend outpatient CR, while 71% will not attend CR. Participants will be excluded if they have any of the following: a clinical diagnosis of uncompensated, severe cardiac failure (Class IV); uncontrolled arrhythmia or angina; severe or symptomatic aortic stenosis; persistent hypotension; a clinical diagnosis of a severe coexisting medical condition that would prevent participation (eg. cognitive impairment, dementia, a terminal illness, severe rheumatoid arthritis, severe arthritis, renal disease requiring dialysis, uncontrolled diabetes); major orthopaedic surgery likely to affect mobility planned within the next 6 months (eg. hip replacement; knee reconstruction; spinal surgery); insufficient English to participate in the telephone coaching calls; non-return of a signed participant consent form and/or a signed doctor's clearance form.

Participants will be recruited six-eight weeks after referral to CR by which time they would be likely to be clinically stable in their recovery process. Brief written information about the study will be included in the information packs distributed to people referred to CR. A personalised invitation letter will also be mailed, followed up with a telephone call.

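### The paired t-tests are not confined to within-arm questions, and the planned between-arm regression leaves out the baseline value and site, at a modest cost in precision

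*Protocol article*

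**What the plan says.** The Statistical analysis section of the Protocol article sets the aim of its bivariate and multivariate analyses, which is to "assess the effects of the intervention (compared to controls) on weight loss, sedentary behaviour, nutrition and physical activity". The model is to be "adjusted for residence (rural or urban), age and sex". For the tests it says: "Continuous data will be analysed with paired t-tests and linear regression". Chi-square tests and logistic regression are named for categorical data. No independent-samples test is named for continuous data.

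Under Randomisation and blinding: "Participants will be block randomized within site", with allocation "by blocks of four to ensure a balanced sample size across both study groups". Under Participants, recruitment is "at two Sydney and two NSW rural hospitals in Australia", so there are four sites. Under Data collection, questionnaires are completed "at baseline, eight weeks and eight months for the intervention group and at baseline, six weeks and six months for the control group", so a baseline value is scheduled for every participant in both arms.

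The abstract gives the primary outcome as weight change, while Outcome measures gives it as self-reported weight and BMI. Study design adds a second role for the control arm, as a replication of an earlier physical activity programme.

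**The concern.** There are two separate matters.

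First, the list of methods follows directly from an aim worded as a comparison with controls. Read in parallel with the categorical methods, the paired t-test takes the place of the unadjusted test of the intervention effect. It cannot fill that place, because it uses one arm at a time. The point has some weight here because both arms receive an active programme, so change from baseline may be expected in both. The Economic analysis section also makes cost-effectiveness ratios depend on which outcomes are statistically significant, so it should be clear which test decides significance.

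Second, the covariate list is explicit. It leaves out the baseline value of the outcome, usually the strongest available predictor of follow-up, and it replaces the four-level randomisation stratum with two-level residence. At stake are precision and the correction of chance baseline imbalance. The validity of the randomised comparison is not at stake.

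**Working it through.** **Inputs from the Protocol article.** 178 per group, 20% loss, difference of 1.3 kg, power 90%, alpha 0.01 (Sample size); analysis level 0.05 (Statistical analysis). Evaluable per arm: 178 × 0.8 = 142.4. **Assumed, because the article gives none:** the between-person SD S, the baseline–follow-up correlation r, the SD of change and any design effect.

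**1. The plan's own figure.** The 178 cannot be reproduced, since neither the SD nor the clustering adjustment is stated. Solved backwards (two-sided, no design effect), SD = 1.3 × √(142.4/2) / (2.576 + 1.282) = 2.84 kg. With a design effect of 2 it is 2.01 kg. One-sided with no design effect it is 3.04 kg. An assumed raw-weight SD of 15 kg would need 2 × 3.858² × 15² / 1.3² ≈ 3,962 evaluable per arm. The sample size therefore looks as if it rests on change in weight, or on weight adjusted for baseline.

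**2. What baseline adjustment gains.** With equal variances at both times, the variances are S² for raw follow-up, 2S²(1−r) for the change score and S²(1−r²) for the baseline-adjusted model. The ratio to the change score is (1+r)/2, and to raw follow-up 1−r².

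| r (assumed) | Cut against change score | Cut against raw follow-up |
|---|---|---|
| 0.4 | 30% | 16% |
| 0.5 | 25% | 25% |
| 0.6 | 20% | 36% |
| 0.95 | 2.5% | – |
| 0.98 | 1.0% | – |
| 0.99 | 0.5% | – |

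The first three rows are the range assumed for physical activity or sitting time. The last three are the range assumed for weight, where the gain over a change score is about 1–3%, or slightly less at r = 0.99. In power terms, with S = 15 kg, 142 per arm and two-sided alpha 0.01, the change score gives 39.5% (r = 0.95) to 99.5% (r = 0.99), and the baseline-adjusted model 40.6% to 99.5%.

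**3. Chance baseline imbalance in weight.** The SE of the baseline difference is 15 × √(2/142) = 1.78 kg. A change score leaves a fraction (1−r) of any imbalance: for a one-SE imbalance, 0.05 × 1.78 = 0.09 kg at r = 0.95 and 0.01 × 1.78 = 0.02 kg at r = 0.99. Both are small against 1.3 kg.

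**4. Separate paired tests read as a comparison.** If both arms truly change equally and each paired test has power p, exactly one arm is significant with probability 2p(1−p). This is 9.5% at p = 0.05, 50% at p = 0.5, 32% at p = 0.8 and 9.5% at p = 0.95. For weight, with an assumed SD of change of 3 kg, 142 per arm and level 0.05, it is 9.5%, 34%, 50%, 33% and 4.6% at true losses of 0, 0.3, 0.5, 0.7 and 1.0 kg. These figures show why a paired test should not stand in for the between-arm test. They apply only if someone uses it that way.

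**5. Site.** Residence carries the urban–rural part of the four-site stratum and leaves out the difference between the two hospitals within each type. Leaving out a balanced stratum does not bias the treatment estimate. It leaves between-site variation in the residual, so standard errors tend to be slightly too large. The article gives no figure from which to size this.

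**The case against.** The strongest reply is that the randomised comparison is already there: the section states a comparison with controls and names an adjusted linear regression. Paired t-tests also have proper uses in this trial. Whether the control arm repeats the earlier programme's result is a baseline-to-follow-up question, and the validation subgroup yields paired self-reported and measured values. All of this stands. What remains is that the section does not say which question the paired test serves.

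Two stronger readings are tempting. A reader might infer that efficacy will be claimed when one arm changes significantly and the other does not, with the error rates in step 4. Nothing in the article says so. A reader might also take the primary outcome in Outcome measures literally and suppose that follow-up weight will be regressed without baseline. With S of 12–18 kg, power for 1.3 kg would then be only about 3–5% at alpha 0.01, against the planned 90%. The documents point away from this: the abstract says weight change, the Statistical analysis section says weight loss, and the SD implied by the sample size is far below any such raw-weight SD. A change score already uses the baseline value, so for weight the omission costs little.

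It can also be said that a condensed article leaves model detail to the full plan. That would answer silence. Here a covariate list is given, and it contains neither the baseline value nor site.

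**Conclusion.** The point holds as a modest and nearly costless improvement to a stated analysis choice. The paired t-test is a within-arm test listed under a between-arm aim without being limited to within-arm questions. The regression that does make the randomised comparison omits the baseline value and the randomisation stratum.

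For weight change the cost is about 1–3% of variance. The main benefit of the change lies in the secondary outcomes with lower correlation, at the 20–30% and 16–36% reductions shown above. Those figures rest on an assumed correlation of 0.4–0.6 and equal variances at baseline and follow-up. Omitting site causes no bias, only a slight conservatism in the standard errors. The documents do not support a conclusion that the trial lacks a valid between-arm analysis, or that its power for weight collapses.

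**What to change.** State that the efficacy test for each continuous outcome is a between-arm linear regression of the follow-up value on arm, the baseline value of that outcome, site (four levels, replacing residence), age and sex, reported as the adjusted difference with its confidence interval. State that paired t-tests serve only within-arm description and the control-arm replication question, and are not evidence of a difference between arms. Paired comparison of self-reported with measured values in the validation subgroup is unaffected.

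The cost is a few lines of analysis text. Baseline values and site are already collected, the model runs in the named software, and the sample size does not change. The different follow-up times in the two arms are a separate matter that this model does not address.
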